**Methods:**

Adults with T2D and a hemoglobin A_1c_ of ≥7 are being enrolled from 14 sites around India. Participants wear a continuous glucose monitor, eat a series of standardized meals, and record all free-living foods, activities, and medication use for a 14-day period. The study’s primary outcome is PPGR, calculated as the incremental area under the curve 2 hours after each logged meal.

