**Inclusion criteria**
Age ≥ 18 and <75 years.Physician-diagnosed type 2 diabetes treated with ≥1 oral hypoglycemic agentsHemoglobin A_1c_≥ 7.0% recorded within the past 30 days.Mobile phone capable of running protocol-specified apps.Functional English literacy.

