**Exclusion criteria**
Unable or unwilling to provide informed consent or comply with the study-specified procedures.Current use of prandial insulin including a continuous insulin infusion pump.Currently pregnant or planning to become pregnant.Estimated life expectancy of ≤12 months.Active cancer.Myocardial infarction or stroke in the last 6 months.Receiving or planned to initiate dialysis for end-stage renal disease.Receiving oral or intravenous steroids.Any contraindication to using a continuous glucose monitor.

Potentially eligible patients are identified from clinic records and are invited to attend an in-person screening visit at which time eligibility is confirmed and written informed consent obtained. Consenting patients are asked to provide sociodemographic and medical information (specifically, age, sex, predominant diet, health conditions, family history, and current medications) and to complete baseline surveys including the World Health Organization’s STEPwise Approach to Non-Communicable Disease Risk Factor Surveillance (STEPS) survey [26], World Health Organization-Five Well-Being Index (WHO-5) [27]. Diabetes Distress Scale [28], Wilson Adherence Scale [29], and the Pittsburgh Sleep Quality Index [30].

Biometric data including blood pressure, heart rate, weight, height, and body measurements at the upper arm, thigh, calf, waist, and hips, are collected by study coordinators at each site. Finally, enrolled participants provide blood samples including a complete blood count, HbA_1c_, blood electrolytes, creatinine, cholesterol, as well as urinalysis.

After completing baseline assessments, participants are fitted with an Abbott Freestyle Libre continuous glucose monitors (CGM) sensor on their upper, nondominant arm and are provided with a Xiaomi Mi Band Smart Wristband (heart rate monitor) and a Roche Accu-Chek glucometer with testing supplies, and dietary supplements to be consumed with their standardized meals (refer to Follow-up Procedures section). Study-specific apps are downloaded on to the participants’ smartphones to allow them to log dietary intake and synchronize their continuous glucose and heart rate monitors. As a back-up, participants are given a paper dietary logbook and a Freestyle Libre CGM reader with which to collect protocol-specified data.

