### Follow-Up Procedures

Participants are followed for 14 days. They are instructed to wear the CGM and heart rate monitor. The heart rate monitor is to be always worn, including during sleep, and only removed for recharging. Participants are also asked to check their capillary glucose on days 2 through 6 before breakfast and dinner.

Participants log their full dietary intake using the study app or logbook over the 14-day study period, including all standardized test meals and free-living foods (including snacks), beverages (including water), and medications. Participants also log all exercise.

Participants are required to consume protocol-specified meals and to perform light activity, as described in Table 1. The standardized meals consist of vegetarian breakfast foods which participants are to prepare in their homes.

The meals vary in their proportion of carbohydrate, fiber, protein, and fat (refer to Table 2).

**Table 1 table1:** Meal schedule during the at-home study period.

Day and timing			Meal type
**1**			
	Breakfast	Fasting	
	Lunch	As desired	
	Dinner	As desired	
**2**			
	Breakfast	Perceived healthy meal	
	Lunch	Post meal exercise	
	Dinner	Typical mixed protein with dinner	
**3**			
	Breakfast	Fiber supplement with standardized test meal	
	Lunch	Premeal exercise	
	Dinner	Alternative mixed protein with dinner	
**4**			
	Breakfast	Fiber supplement before standardized test meal	
	Lunch	As desired	
	Dinner	As desired	
**5**			
	Breakfast	Protein supplement with standardized test meal	
	Lunch	As desired	
	Dinner	Alternative mixed protein with dinner	
**6**			
	Breakfast	Protein supplement before standardized test meal	
	Lunch	Added fiber with lunch	
	Dinner	Alternative mixed protein with added protein	
**7**			
	Breakfast	Regular breakfast	
	Lunch	Added fruit	
	Dinner	Cooled carbohydrate	
**8**			
	Breakfast	Regular breakfast with added protein	
	Lunch	Added fruit with protein	
	Dinner	Regular carbohydrate	
**9**			
	Breakfast	Protein followed by carbohydrate	
	Lunch	Water 30 minutes before lunch	
	Dinner	As desired	
**10**			
	Breakfast	Standardized test meal	
	Lunch	As desired including dessert	
	Dinner	Protein followed by carbohydrates and vegetables	
**11**			
	Breakfast	Standardized test meal with postmeal exercise	
	Lunch	As desired including desert and cinnamon	
	Dinner	Vegetables followed by protein then carbohydrates	
**12**			
	Breakfast	Standardized test meal with postmeal exercise	
	Lunch	As desired	

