During the follow-up period, participants are contacted by phone and text messages to ensure protocol compliance. For participants using the study-specific smartphone apps, a web dashboard is used to monitor the completeness of dietary logging and CGM scanning, with outreach to participants initiated when missing data is detected. Participants using paper logs and a CGM reader, and therefore for whom no dashboard information is available, are contacted daily to ask about protocol compliance. Ad hoc midstudy visits are used to further ensure accurate data collection. If the outreach identifies a problem with a CGM (ie, it was damaged, fell off, or malfunctioned), study staff provide a replacement within 24 hours during which time participants are asked to pause their meal protocol and restart once their CGM has been reapplied and recalibrated. If a test meal was not consumed as intended, participants are provided with the option to repeat the meal.

On day 15, participants are asked to remove their CGM. If need be, study staff help record or correct missing or inaccurate food, activity, and medication data.

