### Statistical Analysis Plan

The study’s primary outcome is PPGR. Following the Wolever and Jenkins method [31], as adapted by Zeevi et al [18], Mendes-Soares et al [20], and Berry et al [32], logged meal times and continuous glucose measurements will be used to calculate the incremental area under the curve. Before conducting analyses, meals logged less than 30 minutes apart will be merged and meals logged within 90 minutes of other meals will be removed. Meals that are very small (<15 g and <70 calories), very large (>1 kg), with implausibly low PPGR values (ie, a PPGR < 5 mg/dL·h after consuming ≥ 40 g of carbohydrates), that are incompletely logged, and which are consumed in the first and last 12 hours of the CGM connection will also be removed. To reduce noise, the median of all glucose values from the 30-minute period before the meal will be taken as the initial glucose level, above which the incremental area will be calculated. Meals that had incomplete glucose measurements in the time window of 30 minutes before and 2 hours after the logged mealtime will be filtered out.

Descriptive statistics will be used to plot the range of PPGRs responses to standardized test meals as well as the correlation between PPGR and the nutritional composition of the logged meals (ie, carbohydrates, fat, and protein).

A machine learning predictor will be developed based on stochastic gradient boosting regression (XGBoost, version 2.2.1; The XG Boost Contributors) [33] using the XGBRegressor class. PPGR will be predicted as the sum of predictions from thousands of decision trees. Trees will be inferred sequentially, with each trained on the residual of all previous trees. The features incorporated in each tree are selected by an inference procedure from features representing meal content (ie, calorie, protein, carbohydrate, and fiber content), meal timing, baseline demographics (ie, age, sex, predominant diet, health conditions, family history, and current medications), baseline survey results (ie, WHO STEPS, WHO-5, Diabetes Distress School, Wilson Adherence Scale, and Pittsburgh Sleep Quality), baseline biometric values (ie, blood pressure, heart rate, weight, height, and body measurements at the upper arm, thigh, calf, waist, and hips), baseline laboratory values (complete blood count, HbA_1c_, blood electrolytes, creatinine, cholesterol, and urinalysis), as well as CGM, heart rate, and activity data.

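### Medication intake is logged for 14 days in a cohort that is all on oral glucose-lowering drugs, but the model takes medication only as a baseline item, so dose intake and timing at each meal are not candidate predictors

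*Protocol article*

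**What the plan says.** All references are to the protocol article.

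- **Treatment at entry.** The inclusion criteria require "Physician-diagnosed type 2 diabetes treated with ≥1 oral hypoglycemic" therapy. Among glucose-lowering drugs, the exclusion criteria name only insulin taken with meals: "Current use of prandial insulin including a continuous insulin infusion pump".
- **Medication at baseline.** Under Eligible Participants and Enrollment, participants report "age, sex, predominant diet, health conditions, family history, and current medications" once, at enrolment.
- **Medication during follow-up.** Follow-Up Procedures has participants log their intake, "including all standardized test meals and free-living foods (including snacks), beverages (including water), and medications". The abstract's Methods agrees: participants "record all free-living foods, activities, and medication use for a 14-day period".
- **Completion of the log.** At the day 15 visit, where needed, "study staff help record or correct missing or inaccurate food, activity, and medication data".
- **Medication in the model.** The Statistical Analysis Plan section lists the candidate features group by group. Medication appears only in the baseline group, "baseline demographics (ie, age, sex, predominant diet, health conditions, family history, and current medications". Adherence enters as a baseline questionnaire score. The features that can vary during the study are meal content, meal timing, CGM, heart rate and activity.

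**The concern.** Postprandial glucose response (PPGR) is computed for each meal, in people whose post-meal glucose is under drug treatment. Whether a dose was taken, and how long before the meal, can differ between two meals of the same person. The study collects this information and has staff complete it, but the listed features give it no route into the model.

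Two things are at stake. Prediction may be less accurate than the data allow. The second aim, identifying factors associated with PPGR differences, is pursued without one plausible within-person factor that is already recorded. The same gap affects the plotted range of responses to standardized meals: without dose status, variation due to treatment on the day cannot be separated from variation between people.

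**Working it through.** The plan gives no figure on this point, so the check is mainly a comparison of what is collected with what is modelled.

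**Step 1. Follow the three self-recorded streams.**

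| Stream | Logged over 14 days | Completed on day 15 if needed | In the feature list |
|---|---|---|---|
| Food | yes | yes | yes, as meal content and meal timing |
| Activity | yes | yes | yes, as activity data |
| Medication | yes | yes | baseline item only |

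The medication log is also given no part in the descriptive analyses or in the assessment of model performance.

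**Step 2. Compare two meals of one participant.** Take the same food at the same hour, once after the usual dose and once after a missed dose. Baseline regimen and adherence score are constant within a person, so every medication feature is identical. Only the CGM, heart rate or activity features could reflect the difference, and only indirectly.

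**Step 3. Remove the indirect route.** The Discussion (Study Implications) makes prediction with no CGM data, or very little glucose data, a key goal. In that version of the model the CGM route is largely gone, and logged dosing would be one of the few direct within-person treatment signals left.

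**Step 4. Look at meal timing.** The protocol itself moves meals. Standardized breakfasts need at least 8 hours of fasting before and 3 hours after. Table 1 sets late breakfasts on days 13 and 14 and dinner finished by 8 PM on days 12 to 14. If participants keep their usual pill times, the dose-to-meal interval shifts with the dietary condition. Meal timing is a feature and dose timing is not, so some drug effect could be credited to timing. This is a possible mechanism; nothing in the documents shows that it operates.

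**Step 5. Illustrate the size under assumptions.** The documents give neither a missed-dose rate nor a dose effect on PPGR. Let p be the share of meals without the usual dose, and d the resulting shift in PPGR, in SDs of the remaining variation. The dose indicator then has variance v = p(1 − p)d², and its share of the total is v/(1 + v).

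- p = 0.05, d = 0.2: v = 0.0475 × 0.04 = 0.0019; share 0.2%
- p = 0.10, d = 0.3: v = 0.09 × 0.09 = 0.0081; share 0.8%
- p = 0.10, d = 0.5: v = 0.09 × 0.25 = 0.0225; share 2.2%
- p = 0.20, d = 0.5: v = 0.16 × 0.25 = 0.0400; share 3.8%
- p = 0.30, d = 0.8: v = 0.21 × 0.64 = 0.1344; share 11.8%

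Each figure is a ceiling for its inputs. It would be lost in full only if regimen, adherence score, meal timing and CGM features captured none of it.

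**The case against.** **The article is a condensed account.** Its parenthetical lists are loose: the meal-content list omits fat, although fat is analysed in the preceding paragraph and tabulated in Table 2, and the CGM, heart rate and activity group is not itemised at all. Detailed feature construction belongs in a full analysis plan, and nothing says the medication log will go unused. This weakens any claim that the log is deliberately excluded. It does not remove the point, because the article does state a specification: it takes food and activity into the model and places medication at baseline.

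**Dose status may be unknown when a diet is prescribed.** The sample size section describes prediction from individual characteristics, so a model built on stable patient and meal features is defensible. This stands as a reason to report such a model. It is no reason to leave dosing out of the candidate set when factors associated with PPGR are also sought.

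**Stronger readings that a reader might infer.**

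- *Treatment is ignored.* It is not: baseline regimen and an adherence scale are features, and CGM data may carry part of the effect.
- *Drug effects are being attributed to foods or time of day.* This would need off-dose meals, or shifted dose intervals, to coincide systematically with particular foods or times. Step 4 shows how that could happen, not that it does.
- *The loss is comparable with the 2% to 3% of variance in the sample size section.* The 2.7% there is explicitly variation between individuals, whereas the loss here is between meals within a person. That section sets no threshold for the latter.

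**Conclusion.** The point holds in a limited form. As the article specifies the model, meal-level medication intake and dose timing are not candidate predictors of a meal-level outcome, although they are recorded for a cohort in which everyone is on oral treatment. The consequence is residual within-person variation that the model cannot explain directly, most plainly in the version without CGM data.

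The size cannot be derived from the documents. The 0.2% to 11.8% range depends wholly on the assumed p and d and on a single common shift in PPGR, and each value is a ceiling. The conclusion itself does not depend on these figures; it rests on the feature list set against the data collected. Bias towards meal timing or food remains possible and undemonstrated.

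**What to change.** Add to the candidate features in the Statistical Analysis Plan section, derived from the existing medication log:

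1. the drug class taken;
2. the time from the last logged dose to the meal;
3. whether the usual dose was logged that day, stating whether entries after the meal count.

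Keep baseline medications and the adherence scale. Report performance both with and without the three features, since dose status may be unknown when a diet is prescribed. If the log is not to be used, say so and give the reason.

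The cost is some coding of data already collected, with no new visits or measurements. The drawback is reliance on a self-reported log: a missing entry is not proof of a missed dose, so unrecorded should be kept distinct from not taken where the log allows.

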### Study Setting

This trial is being conducted at 14 outpatient clinics in geographically distinct regions across India with population sizes ranging from 1.2 to 34 million. Sites were identified and managed by IQVIA, a multinational contract research organization, and were included if they specialized in the care of individuals with diabetes, had an established research infrastructure for the conduct of diabetes-related studies including a site principal investigator who is a diabetologist (with clinical training in endocrinology or internal medicine), a local ethics committee to provide study oversight, and a sufficient volume of potentially eligible patients. Study enrollment began in May 2022.

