Performance will be assessed by holding out 30% of the sample and using 5-fold cross-validation in which cross-validation participants are divided into 5 groups, the model will be trained on the other 4 parts. Random datasets of the same size as the original will be sampled with replacement from the original dataset, and the entire training and validation process will be repeated. The performance will be measured by the ability to accurately predict meals reported by the held-out participants. Prediction results will be aggregated, and Pearson product moment correlation with the measured PPGRs will be reported. The SE for the calculated performance will be assessed using at least a thousand iterations of bootstrapping until the errors stabilize. Model discrimination will be assessed using a binary cut-point for PPGR, set at the 50th percentile of all observed PPGR values, plotting a receiver operating characteristic curve (ROC) and then calculating the area under the ROC.

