There is exceptionally limited data for variability in PPGR for individuals with T2D in the peer-reviewed although it is highly likely that such variability exists [22]. The primary goal of our study is to fill this void and to generate an India-specific machine-learning models on the basis of which PPGR can be predicted with high accuracy for T2D. Similar models have been built in other jurisdictions. For example, a machine learning algorithm trained on CGM data, dietary, activity, anthropometrics, and gut microbiota for nondiabetic individuals in Israel was much more accurate at predicting PPGR than generic models based on the carbohydrate content or the amount of calories in a meal [18]. A separate US-based study had similar findings [20].

Among individuals with diabetes, a study in the Netherlands that included a small number of individuals with T2D along with individuals with prediabetes and normal glucose metabolism, a machine learning model based on CGM data was highly accurate in predicting future glucose values but this study did not specifically evaluate the ability to predict PPGR [41]. A US study of 1000 patients of whom 1-quarter had T2D found that a machine learning model trained on CGM, HRM data and food logs was highly accurate at predicting PPGR but this study has, to our knowledge, only been published in abstract form [22]. These studies have all relied on CGM data to make their predictions. While these devices are increasingly used, practice guidelines do not recommend their long-term use for most individuals with T2D [42]. Accordingly, a key goal of our study will be to explore the ability to predict PPGR response without reliance on CGM data or with very limited blood glucose data from patients.

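### The planned accuracy applies to new patients at the same 14 clinics; nothing planned shows how the model transfers to a clinic it has not seen

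*Protocol article*

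**What the plan says.** **Validation (Statistical Analysis Plan).** The scheme is internal and works on participants: "Performance will be assessed by holding out 30% of the sample and using 5-fold cross-validation in which cross-validation participants are divided into 5 groups". The test is on people not used in training: "The performance will be measured by the ability to accurately predict meals reported by the held-out participants". Uncertainty comes from the study's own data: "Random datasets of the same size as the original will be sampled with replacement from the original dataset". Reporting is pooled: "Prediction results will be aggregated, and Pearson product moment correlation with the measured PPGRs will be reported". One area under the ROC curve is added, using a median cut-point. No result by clinic, no hold-out by clinic or region and no outside cohort is mentioned.

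**Where participants come from (Study Setting).** "This trial is being conducted at 14 outpatient clinics in geographically distinct regions across India". The clinics were selected, not sampled: they "were included if they specialized in the care of individuals with diabetes, had an established research infrastructure".

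**What the model is for (Study Implications).** The aim is "to generate an India-specific machine-learning models on the basis of which PPGR can be predicted with high accuracy for T2D".

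**Limits conceded (Limitations).** The article restricts generalisability because recruitment is through diabetes clinics and requires English literacy and a suitable phone. It does not name clinic or region as a limit.

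**The concern.** A test on held-out people measures accuracy in the setting from which those people were drawn. If each clinic contributes to both training and test, anything the model learns about that clinic is rewarded in testing. At a new clinic that knowledge is worthless or misleading.

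The article describes several routes by which clinic-related patterns could enter:

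- Body measurements and blood pressure are taken by coordinators at each site (Eligible Participants and Enrollment) and are model features.
- Test meals are prepared at home, and many other meals use the participant's usual foods (Follow-Up Procedures), so foods and the way they are logged may differ by region.
- Predominant diet and current medications are features and may partly stand in for region or clinic.

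Clinic itself is not a listed feature, so these are indirect routes through predictors and food logging. The outcome is a different matter, because a single CGM model is named for participants.

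At stake is the meaning of the headline figure. A reader who sees a high correlation for an India-specific model may assume that it holds at the next clinic. No planned figure tests that, and the model is meant to inform personalised diets.

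**Working it through.** The article states no figure on this point, so none is in dispute. The check asks what the planned estimate measures.

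**1. Inputs.** There are 14 clinics (Study Setting). The recruitment target is 1050, with 5% loss and 1000 evaluable (Sample Size Considerations). The hold-out is 30% (Statistical Analysis Plan). The evaluable number reproduces: 1050 × 0.95 = 997.5, or about 1000.

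**2. People per clinic.** Assuming equal clinics:

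- evaluable: 1000 / 14 = 71.4
- held out: 300 / 14 = 21.4
- training: 700 / 14 = 50.0

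**3. Chance that a clinic is unseen.** Assume also that the 300 are drawn at random from the 1000. For a clinic of 71, the probability that all 71 fall in the hold-out is C(929, 229) / C(1000, 300), about 1.2 × 10⁻⁴⁰. In practice 0 of 14 clinics would be absent from training. Clinics of somewhat unequal size would not change this conclusion.

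**4. Possible size of the optimism.** This needs the share of PPGR variance attributable to clinic, which the article does not give. As an illustration only, suppose the transferable signal explains 40% of total variance and clinic explains a further share *s*. If the model recovers the clinic part completely (an upper bound), the pooled correlation at seen clinics is √(0.40 + *s*). At new clinics it is √0.40.

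| Assumed clinic share *s* | Seen clinics, at most | New clinics |
|---|---|---|
| 0% | 0.63 | 0.63 |
| 1% | 0.64 | 0.63 |
| 5% | 0.67 | 0.63 |
| 10% | 0.71 | 0.63 |

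On these assumptions the gap runs from nothing to at most 0.08 (0.707 − 0.632 = 0.075).

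**5. Uncertainty hidden by a single pooled figure.** If the clinic-level correlations have standard deviation *d*, a 95% prediction interval for one new clinic, based on 14 clinics, has half-width t(0.975; 13) × *d* × √(1 + 1/14) = 2.16 × 1.035 × *d*. For *d* = 0.03, 0.05 and 0.10 (assumed) this is ±0.07, ±0.11 and ±0.22. A pooled correlation with a bootstrap standard error does not report this spread.

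**The case against.** **The plan is coherent as it stands.** Holding out whole participants avoids the serious error of having one person's meals in both training and test. Nothing in it is contradictory or miscalculated. This stands; the point concerns the scope of the estimate.

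**Validation by clinic may be in a fuller analysis plan.** A journal article condenses. Here, however, the article itself fixes the unit of splitting and the pooled metrics, so the choice is open to comment.

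**A reader might infer that the planned accuracy cannot support an India-wide predictor.** The article does not support that reading. It says India-specific, in contrast to models built in other countries, and nowhere claims that the hold-out will prove accuracy at unseen clinics. Testing on new people across 14 clinics in distinct regions is real, though limited, evidence.

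**A reader might infer that failure in one region would be invisible.** That is also too strong. Under step 2 each clinic supplies about 21 test participants. Using the article's 42,000 meals, that is 42,000 × 0.30 / 14 = 900 logged meals per clinic before exclusions. The planned results could be broken down by clinic; the article simply states an aggregate.

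**A reader might infer that the glucose outcome is measured differently from clinic to clinic.** The article gives no sign of this. One CGM model is named, and one organisation manages all sites. Help with completing logs is attributed to study staff, with no suggestion that it varies by clinic.

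**The random draw is an inference.** The article does not say how the 30% is chosen, so a draw by clinic is not strictly excluded. The references to dividing participants and to held-out participants make it unlikely.

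**Conclusion.** The point holds as a limit on inference. The planned correlation and area under the curve estimate accuracy for new patients at these 14 selected clinics. They do not by themselves show transfer to other clinics or regions, and the Limitations section does not mention this although the stated aim is an India-specific model with high accuracy.

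This conclusion assumes that the 30% is drawn by participant. The count of 0 unseen clinics out of 14 further assumes a random draw and roughly equal clinics. The direction of any error would be optimism, but its size cannot be derived from the article and may be near zero; the figures in steps 4 and 5 of the working are illustrations on assumed inputs. This is a worthwhile, inexpensive improvement and not a fatal flaw.

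**What to change.** Keep the planned participant-level split and add leave-one-clinic-out (internal-external) validation. Train on 13 clinics, with any tuning done inside those 13, test on the fourteenth, and repeat for all 14. Then:

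- Report performance for each left-out clinic with its between-clinic range.
- Also pool the left-out predictions into one correlation for comparison with the planned one. A correlation within one clinic cannot detect a shift in that clinic's mean.
- Base any claim of accuracy beyond the participating clinics on these results.
- Word the participant-split figure as applying to new patients at participating clinics.
- Name transfer to other clinics and regions in the limitations.

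The cost is 14 further model fits and some analysis wording; no new participants or data are needed. The unseen-clinic figure may be lower, and it will be less precise because it rests on 14 clusters. Each of these fits trains on about 929 people (1000 × 13/14) against about 700 in the planned split, so the gap between the two figures is not purely a clinic effect.

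Replacing the 30% hold-out with 4 whole clinics (4/14 = 28.6%) is not advised. It would rest the headline on 4 clusters, make it depend on which 4 were picked, and leave 10 clinics with no one in the final test.
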